#### Analysis to address Aim 2: identify factors associated with financial distress over time

We will use univariate mixed models to identify factors independently associated with the continuous PFWS score over time. We will employ multivariate mixed models and backward selection methods to identify factors jointly associated with the PFWS score; non-significant predictors will be excluded (if *p* >  = 0.05) to produce a final model. We will consider time (T1, T2, T3) as a 1 degree of freedom (df) variable in the model. Significant predictor interaction with time will be considered in the final multivariate model. We will evaluate and address multi-collinearity during model selection. Factors that we will consider include socio-economic variables, clinical variables, institutional variables, material hardship variables (annual household income, a continuous variable and HMH score, a categorical variable), and financial coping behaviors.

#### Analysis for exploratory aims

We will use descriptive statistics to report domains of financial distress informed by the conceptual framework. We will assess treatment-related material hardship as a) change in HMH score, b) percent change in annual household income, c) change in % FPL category, d) consideration of or actual filing for bankruptcy, and e) parent-reported out-of-pocket costs. We will assess potential coping behaviors by parent report of resources used and modification of financial or psychological behaviors. We will describe institutional factors associated with parent-reported financial distress, including the number of social workers, availability of philanthropic support (yes/no), and availability of financial advisor/navigation (yes/no). We will use institutional factor measurements via institution surveys obtained closest to the timing of the parent assessment.

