Both child and cancer characteristics may also impact the risk for financial toxicity. Acute lymphoblastic leukemia (ALL), the most prevalent type of cancer in children and curable in more than 90% of children, requires treatment that is intense and lengthy [9]. For example, most children with ALL require more than 2 years of cancer treatment to achieve cure but some treatment (such as intrathecal chemotherapy) can only be provided by specialized cancer treatment centers, thus incurring more costs for those who live distant from a treating center. Similarly, tumor genetics and disease response to therapy are used to guide risk-adapted therapy, such that children with high or very-high risk tumor genetic profiles or poorer response to initial therapy receive more intensive, hospital-based therapy than those with low-risk tumor genetic profiles or better response to initial therapy [10–12]. Beyond tumor genetics and initial disease response, patient race, ethnicity and socioeconomic status are independently associated with survival outcomes in ALL secondary to social determinants of health that may be amenable to care delivery and policy level interventions. (Gupta et al. ASH 2021, manuscript in preparation) [13–19].

Oral chemotherapy is the mainstay of the maintenance phase of ALL therapy [20]. Significant caregiving efforts are regularly required of parents to optimize their child’s adherence to oral medications, which—together with lengthy treatment and the associated financial burden—is a significant source of psychosocial stress [21, 22]. Newer targeted therapies, such as tyrosine kinase inhibitors or immunotherapy, [23] may substantially increase the cost of therapy for children with higher-risk ALL. The financial burden of accumulating treatment-related costs, along with declining household income due to treatment-associated parent work disruptions to provide caregiving, generates continual or cyclic financial distress [8].

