## Main text

### Methods

Our study will use a prospective cohort design with an embedded optional qualitative study for a sub-cohort of participants. Parents participating in the cohort study will complete surveys at three time points (T) during the index child’s treatment—during induction therapy (T1), during maintenance therapy (T2), and around the time of completion of treatment (T3). For the sub-cohort of parents who agree to participate in the qualitative study and are selected, we will conduct an individual interview between T1 and T3. We will also ask research personnel at institutions that enroll at least one parent on the study to complete an annual survey of institution-level information. Details of the study design are shown in Fig. 2. The study is registered with the NCI (identifier NCI-2021–03,567) and was approved by the NCI Pediatric Central Institutional Review Board (CIRB).

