We will use 5 indicators to assess *material hardship*: (a) change in household material hardship (HMH), (b) change in parent-reported household income, (c) categorical change in percent federal poverty level (%FPL), (d) new consideration of or actual filing for bankruptcy, and (e) out-of-pocket expenses. Indicators of HMH include food, housing, transportation, and energy insecurities, which are amenable to interventions such as matching individuals with concrete resources (food assistance, travel supports) [19, 27, 37]. HMH is a proxy for poverty-exposures and, as a modifiable metric, may be a more useful indicator of SES than household income [37, 38]. We will use five items from the abbreviated form of the 13-item Oncology Economic Impact Study survey to assess food, housing, energy, and transportation insecurities [29]. HMH will be categorized by domain (endorsing food, housing, energy, or transportation insecurity) on a scale of 0 (no domains endorsed) to 4 (all four domains endorsed), and scored as a categorical variable (number of unmet material needs, range 0–4). We will collect *household income* as a continuous variable and use the data to calculate percentage change in income between time points. Catastrophic reduction in income related to medical expenses has been defined as a reduction exceeding 40%; more than 10% reduction can tip families into poverty [39, 40]. We will also examine household income and household size relative to the federal poverty level (FPL) for the data collection year, per the US Health and Human Services Poverty Guidelines [41]. Income poverty is defined as less than 100% FPL and low-income as less than 200% FPL, which is commonly used to determine eligibility for government programs such as public health insurance and food assistance. We will categorize % FPL as less than 100% FPL, between 100 and 200% FPL, between 200 and 300% FPL, and more than 300% FPL. We expect that about 20% of the index children and their parents will be living in poverty at diagnosis [42, 43]. We will use two items in the follow-up surveys (T2, T3) to assess new onset of consideration of or actual filing for bankruptcy. Similarly, we will use two items to assess direct (out-of-pocket expenses) and indirect (opportunities lost) costs. We will also explore direct and indirect costs in qualitative interviews with the participating study sub-cohort.

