We will assess *financial coping behaviors* by asking parents to indicate how often (never, sometimes, often, or I don’t have this resource) they used 12 strategies to accommodate the costs associated with the child’s cancer care. The listed strategies include changes in health-related behaviors (forgoing recommended or needed health care for the index child or another family member) and changes in financial behaviors (accumulating credit card debt), similar to items used in prior studies of parents of children diagnosed with cancer [44]. We will also assess (yes, no, no-not eligible, no-I don’t know if I’m eligible) if the parent accessed financial resources, including from the government, the treating institution, and/or philanthropic organizations (Table 1).

**Table 1 Tab1:** Modifiable secondary outcomes amendable to individual or healthcare delivery interventions

Aim	Measure	Objective	Analytic Plan	Modifiable target/future intervention
Aim 1	Personal Financial Wellness Scale	Determine trajectory of financial distress	Mixed model	Financial distress may be amenable to financial navigation (Shankaran, 2018) and other types of intervention
Aim 2	Personal Financial Wellness Scale	Identify socio-demographic, clinical, financial and institutional factors associated with financial distress over time	Mixed model	Predictors of financial distress will inform identification of at-risk groups to target with future interventions
Aim 2	Household income relative to the Federal Poverty Level (%FPL) Household Material Hardship (HMH) Bankruptcy Out-of-pocket costs	Describe treatment-related material hardship during treatment for pediatric ALL as assessed by 1) worsening or new HMH, 2) percent change in annual household income, 3) change in % FPL 4) consideration of or actual filing for bankruptcy and 5) parent-reported out-of-pocket costs	Descriptive statistics	Worsening HMH is amenable to resource-matching interventions (Garg, 2007 & 2015). %FPL and out-of-pocket costs may predict risk for and characterize HMH
Aim 2	Coping behaviors survey	Describe parent financial and health coping behaviors	Descriptive statistics	Parent coping behaviors such as cutting back on needed health care due to cost may be amenable to behavior change interventions Lack of information about available resources or not following through on referrals may be amenable to resource-matching and/or financial navigation

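### Before-after changes in hardship, income and %FPL are called treatment-related in a single cohort without a comparator, and the income and %FPL indicators rest on different bases, so they can disagree

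*Protocol article*

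**What the plan says.** The section on analysis for exploratory aims reads: "We will assess treatment-related material hardship as a) change in HMH score, b) percent change in annual household income". The list goes on to change in %FPL category, bankruptcy and out-of-pocket costs. Table 1 uses the same label: "Describe treatment-related material hardship during treatment for pediatric ALL as assessed by 1) worsening or new HMH, 2) percent change in annual household income".

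The Methods describe one cohort: "Our study will use a prospective cohort design with an embedded optional qualitative study for a sub-cohort of participants". No comparison group, external trend or rule for attributing a change to treatment is described for HMH, income or %FPL. T1 falls in induction and T3 around the end of treatment, and the Introduction says that "most children with ALL require more than 2 years of cancer treatment to achieve cure".

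The Parent survey section defines the two income-based indicators. For income, the study will "use the data to calculate percentage change in income between time points"; no price adjustment is mentioned. For poverty level, it will examine "household income and household size relative to the federal poverty level (FPL) for the data collection year", in four categories with cut-points at 100, 200 and 300% FPL.

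**The concern.** There are two problems.

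**Attribution.** A change between T1 and T3 in one cohort is the sum of what the child's treatment did to the household and everything else that happened to it over the same period: price rises, the job market, a birth or a separation. Without a comparator or an attribution rule the parts cannot be separated. Calling the total *treatment-related* claims something that the data cannot show. Table 1 presents these measures as targets for future interventions, so readers will probably take the label at face value.

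**Two bases.** As written, percent income change compares reported dollars at two dates. The %FPL denominator is replaced with each collection year's guideline. If guidelines rise over follow-up, a family whose reported income has not moved can show no loss on one indicator and a worse category on the other. A reader of the results table could not tell whether such a family became worse off.

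**Working it through.** The plan gives no figure of its own on this point, so there is none to reproduce.

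**Label against design.** Set side by side:
- Label: *treatment-related*, in both Table 1 and the exploratory analysis.
- Design: single prospective cohort (Methods).
- Interval: more than 2 years for most children (Introduction).
- Analysis: descriptive statistics of change, with no comparator or attribution rule described.

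The last three support a statement about change during treatment. They do not support a statement about change because of treatment.

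**Income against %FPL.** Inputs:
- *y* = proportional change in reported income, T1 to T3.
- *g* = growth of the poverty guideline over the same interval. It is not in the documents. I assume annual rate *i* over *t* years, so 1 + g = (1 + i)^t, and I assume that prices rise at the same rate.
- Household size constant.
- Cut-point C = 100, 200 or 300 (Parent survey section).

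Formulas:
- Ratio of end to start %FPL = (1 + y)/(1 + g).
- When this ratio is below 1, the category worsens across C if the starting %FPL lies from C up to C(1 + g)/(1 + y).
- Real income change = (1 + y)/(1 + g) - 1.

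With unchanged reported income (y = 0), at the 200% cut-point:

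| Assumed growth | 1 + g | Percent income change as planned | Real loss, 1 - 1/(1 + g) | Starting %FPL that falls below 200 |
|---|---|---|---|---|
| 0% | 1.000 | 0% | 0% | none |
| 2% a year, 2 years | 1.040 | 0% | 3.9% | 200-208 |
| 3% a year, 2.5 years | 1.077 | 0% | 7.1% | 200-215 |
| 5% a year, 2.5 years | 1.130 | 0% | 11.5% | 200-226 |
| 6% a year, 3 years | 1.191 | 0% | 16.0% | 200-238 |

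Example at 3% a year over 2.5 years: a family starting at 210% FPL ends at 210/1.077 = 195%. Its income change is recorded as 0% and its %FPL category as worse. The same happens just above the other cut-points: 100 × 1.077 gives 100-108%, and 300 × 1.077 gives 300-323%.

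**Effect of a common basis.** If T3 income is put in T1 dollars with a deflator that grows as the guideline does, its change is (1 + y)/(1 + g) - 1. With constant household size this is exactly the proportional change in %FPL. The family in the example would show -7.1% on income, in line with its fall from 210% to 195%. A published price index need not track the guideline exactly, so agreement would be close but not guaranteed.

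**The case against.** **The results are exploratory and descriptive.** No test or causal estimate is planned, and Table 1 already contains the phrase about treatment for pediatric ALL. The intervention it names for HMH, matching families to resources, addresses need whatever its cause. This limits the consequence but does not rescue the label, because a descriptive result under a causal name is still open to misreading.

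**Price adjustment is a derivation detail that an article may leave to the analysis plan.** This is fair. That income is unadjusted is inferred from silence, and the survey itself (Additional file 1) is not shown, so the income reference period and any attribution wording in the items cannot be checked. The article does fix the year-specific basis for %FPL, however, and it says nothing to put income on a matching one.

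**Two yardsticks can be complementary.** This stands as far as %FPL is concerned. The plan notes that %FPL levels commonly decide eligibility for public programs, so the current guideline and household size belong in that measure, and it should not be re-based.

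Stronger readings are tempting, but the documents do not support them:
- *That the two indicators give opposite answers.* In the example one shows no change and the other a decline, which is disagreement and not reversal. Opposite signs need an income rise smaller than guideline growth (0 < y < g), and an opposite category result also needs a start just above a cut-point. For instance, with g = 10% and y = 5% the start must lie at 200-209.5%. If income falls, household size is constant and guidelines do not fall, both indicators move down.
- *That every fall is counted as hardship.* The text lists change measures and fixes no such rule. On the 0-4 HMH scale a fall is an improvement, and Table 1 speaks of worsening or new HMH.
- *That 10% and 40% income losses are the plan's cut-offs.* They are cited as background, and nowhere does the plan say it will apply them.
- *That %FPL overstates loss.* If prices rise, flat dollars are a real loss, and the year-specific %FPL registers it.

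**Conclusion.** The point holds on both counts, within limits.

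The attribution problem follows from the text and needs no assumption: before-after changes in HMH, income and %FPL category are labelled as treatment-related in a design that cannot attribute them.

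The disagreement between income change and %FPL is possible but conditional. It rests on guideline growth, which the documents do not give, and on income not being adjusted for prices. Over the assumed range of 2-6% a year for 2-3 years, the band of families affected above the 200% cut-point runs from 200-208% to 200-238%, and it vanishes at zero growth. The number of families in these bands cannot be derived, because the only information on starting %FPL is that about 20% are expected to be living in poverty.

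The effect is confined to exploratory, descriptive results. The PFWS primary analysis is untouched. The change is worth making because the label governs what the study may be taken to conclude, and correcting it costs very little.

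**What to change.** 1. In Table 1 and in the exploratory analysis, for the three change measures (HMH, household income, %FPL category), replace *treatment-related material hardship* with *change in material hardship during treatment*. State that no attribution to treatment is made.
2. Report percent income change in constant T1 dollars, using a named published price index, beside the unadjusted change.
3. Keep %FPL on the collection-year guideline and current household size, as planned.

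Income is already collected and the survey year is known, so no new data are needed. The cost is a few lines of extra analysis and a less causal label.

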#### Analysis to address Aim 3: explore parental experiences of financial distress, material hardship, and perceptions of financial screening during their child’s ALL treatment

We will secure verbatim transcripts of each audio-recorded interview in the source language, that is, in English for interviews conducted in English and in Spanish for interviews conducted in Spanish, the associated field notes and an interview summary. We will analyze these data using a directed content analysis approach and codebook of predetermined codes derived from our conceptual framework. Following a rigorous process and staying in the source language as much as possible to avoid losing meaning in translation, [47–50] two study team committee members trained in qualitative analysis will code each English language transcript, and two bi-lingual study committee members trained in qualitative analysis will code each Spanish-language transcript. These individuals will inductively code data segments that don’t fit predetermined codes by adding labels, definitions, and examples of data segments that reflect inductively derived codes to the codebook for use in future coding, then re-examining already coded data for examples of the new codes. Two bi-lingual individuals familiar with cultures of Spanish-speakers will work side-by-side to translate the concepts, categories and themes that emerged from the Spanish-language transcripts into English, with illustrative quotes in both the source language and English [50]. Study committee members trained in qualitative methods will use these translations in further analyses (e.g., comparing and contrasting concepts, categories and themes) of the entire qualitative data set. Once saturation is reached and no new themes are emerging from interviews conducted in Spanish or in English, our study team will agree on and synthesize the final themes. We will provide quotes in the source language in research reports of the work to address aim 3 [51].

### Participant retention and data quality considerations

We have a plan for close data monitoring and optimization of participant retention. We will identify missing parent survey data at the earliest possible time point, following the closure of the assessment window/expiration of survey link. We will run regular queries to identify missing assessments as well as missing data within the assessments. We will engage research personnel at the enrolling institution to assist us in determining the reason for missing assessments (e.g., illness, forgot, unable to make appointment). A study committee member will review completed surveys to identify missing items, and send reminders to parents and institutions via secure REDCap® link to encourage completion of missing items as soon as possible within the assessment window. If the T1 survey is missing, we will not include the parent in any analysis. However, if the T2 or T3 survey is missing, we will collect the reason for missing data with assistance from research personnel at the enrolling institution and may use the data as outlined in the statistical plan. We will also work closely through the NCORP network, including regular virtual meetings with COG research personnel at participating institutions, to discuss missing data and address challenges as proactively as possible. The NCORP network has been utilized in prior studies through COG and was successful in obtaining high-quality data.

## Discussion

From what is known at this point in time, no studies have prospectively examined trajectories of financial distress during ALL treatment. Our study aims to address this gap utilizing the existing robust research infrastructure of NCORP to enroll a diverse parent cohort based on language, geography, socioeconomic status, and self-identified race and ethnic categories to support the generalizability of our findings. Results of this investigation will be highly salient to a wide range of stakeholders given the potential associations between financial distress, treatment adherence, care outcomes and quality of life in pediatric ALL, the most common pediatric cancer. Upon study completion, we anticipate a robust understanding of how financial distress evolves during ALL therapy to inform rigorous studies in the future to accurately identify and intervene on this potentially catastrophic adverse effect of cancer care. We briefly discuss procedural, human subjects, and analytic considerations, and speculate about implications and future goals informed by this study.

### Procedural considerations

We recognize the time and resource commitment required for participation in clinical research. Though the participating institutions have infrastructure funded in part through the NCORP, observational or supportive care studies are reportedly not prioritized by institutions as often as treatment clinical trials [52, 53]. We therefore aim to operationalize a feasible and scientifically robust study to ensure collection of high-quality data by addressing multi-level factors known to contribute to study burden and thus negatively affect recruitment and retention of diverse samples in research of cancer populations [54, 55]. For example, the study will be conducted at NCORP institutions where racial/ethnic minorities and other under-served groups tend to seek care. Moreover, NCORP site research staff are trained in how to approach potential participants about studies for which they are eligible. By utilizing the REDCap® platform and other technologies, we expect to mitigate logistical challenges by (a) contacting parents directly using their preferred method and removing this burden from research staff at the enrolling institution, (b) letting parents complete the study surveys at their convenience and designing the surveys so they can pause/resume their work as needed, and (c) developing survey and data tracking procedures that use a multidimensional process to integrate data from the CTSU OPEN enrollment portal with data from REDCap® and Medidata Rave. We conducted a series of tests with the study committee in collaboration with parent stakeholders from the COG Patient Advocate Committee (PAC) to validate assumptions underlying our processes for data collection and minimization of missing data.

